## **Introduction**

Obstructive Airway Diseases (OADs) such as asthma and COPD are now major health issues for Australia. Airway inflammation is recognised as a key element of airway disease, but its role is poorly understood. Persistent neutrophilic airway inflammation (neutrophilic bronchitis) is considered a typical feature of COPD and we have recently described a subgroup of patients with asthma who also have neutrophilic inflammation. Each of these conditions is associated with airflow obstruction. Importantly, we found that the mechanisms underlying the development of airway neutrophilia were similar and remarkably consistent across the different conditions. We found that the induction of neutrophilic bronchitis involved upregulation of gene expression and protein secretion of the potent neutrophil chemoattractant IL-8 (CXCL8) (1), as well as neutrophil protease release.

There is a need to identify effective treatment options for people with OAD and neutrophilic inflammation. The anti-inflammatory effects of macrolides include the inhibition of inflammatory cytokines such as IL-8 (4), reduced activation of neutrophils and enhanced phagocytosis of apoptotic neutrophils (5). The discovery of these anti-inflammatory properties *in vitro* led to the investigation of macrolide antibiotics in the treatment of airway diseases such as diffuse panbronchiolitis (6) where similar reductions in neutrophils and IL-8 levels were observed. Macrolides have also been shown to lower IL-8 levels in chronic sinusitis (7) and are effective anti-inflammatory agents in cystic fibrosis showing improvements in quality of life and prevention of the deterioration of lung function (8). We have recently shown that macrolide antibiotic use in asthma can reduce IL-8 levels and improve quality of life (9).

Macrolide antibiotics such as azithromycin (AZM) are concentrated in host cells such as macrophages and neutrophils and have been shown to have anti-inflammatory effects. Azithromycin is a 15-membered ring macrolide derivative of erythromycin. It has a number of advantages over erythromycin including fewer side effects and also the possibility of once daily dosing due to its long elimination half-life.

We propose to conduct a randomized double blind placebo controlled treatment trial in participants with neutrophilic airway disease (asthma or COPD) to investigate the anti-

inflammatory effect of AZM on airway inflammation. The primary outcome of this trial will be reduced levels of IL-8 in sputum, however other outcomes will also be assessed such as neutrophil numbers (%), sputum bacterial load (colony forming units/mL), levels of neutrophil elastase. Clinical outcomes will also be determined including symptoms, lung function and quality of life (St George's Respiratory Questionnaire) and severe exacerbations. Participants will be recruited to attend a screening visit, and if stable, they will enter a 2-week run-in period and then be randomised to either AZM (250mg) or placebo daily for twelve weeks. Study visits will occur at monthly intervals where symptoms, lung function and induced sputum will be assessed. A post treatment visit will be conducted 4 weeks after the end of treatment and then we will contact participants by telephone to monitor their airways disease and see if they have had an increase in their symptoms or medication use (exacerbation). We will monitor patients symptoms and medication use for a total of 6 months from their enrolment in the study.

*Sample size* - In a recent study, the effect of clarithromycin in COPD (10) was found to reduce sputum IL-8 levels from 1606 (367) to 882 (144) pg/mL. We will recruit 40 participants (this includes a 10% withdrawal rate) which will give sufficient power (80%) to detect a change in IL-8 levels in the order of 250pg/mL (alpha 0.05).

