## **Study Design**

This is a double blind placebo controlled study. This study will last for 6 months and involve a minimum of 6 visits to the research unit and telephone consultations.

[figure not shown]

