### *Patient Allocation*

Patients will be randomly allocated to either receive placebo or AZM 250mg daily. They will take the medication for twelve weeks. Both the participant and the investigators will be blinded to the intervention until the conclusion of the trial. The placebo and agent will be packaged similarly and have identical taste. The use of other medications will be assessed at the commencement of the trial and updated with each contact. The patient will be asked about all new medications commenced and changes in the use of regular medications. If a participant commences treatment with other antibiotic agents during the study they will be withdrawn from the study. To aid compliance medication will be dispensed at each visit. Participants will also be questioned about compliance during the regular phone review.

Treatment will be randomised using random permuted blocks of 6. The data manager in the respiratory research unit using the Randomisation Generator Software (11) will generate the randomisation allocations. The randomisation tables for each stratification list will be

provided to the pharmacy department who will dispense active or placebo medication according to the schedule. The investigator and research team working with the participants will not have access to the randomisation schedule during the study.

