### **Evaluation of the Study**

The primary outcomes will be:

- Decrease in sputum IL-8

Secondary outcomes will be:

- Decreased in airway bacterial load
- Decreased sputum neutrophils
- Decrease in bronchial wall thickening on chest CT scan
- Number of exacerbations during follow-up

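### The stated 80% power for about 250 pg/mL needs an IL-8 SD of at most about 260, which the protocol does not state and its cited figures do not support for an unadjusted between-arm test

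*Protocol*

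**What the plan says.** The sample size paragraph at the end of the Protocol's Introduction rests on one earlier study of clarithromycin in COPD, which "was found to reduce sputum IL-8 levels from 1606 (367) to 882 (144) pg/mL". It then states: "We will recruit 40 participants (this includes a 10% withdrawal rate) which will give sufficient power (80%) to detect a change in IL-8 levels". The same sentence puts that change at about 250 pg/mL, with alpha 0.05.

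The trial is a randomised comparison with placebo. Study Design says "This is a double blind placebo controlled study", and Patient Allocation says "Patients will be randomly allocated to either receive placebo or AZM 250mg daily". The primary outcome under Evaluation of the Study is "Decrease in sputum IL-8".

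The paragraph does not give the SD used, the test, its sidedness, or whether the change is within or between arms. It does not say what the bracketed values are. The allocation ratio is not stated either.

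**The concern.** The paragraph makes a specific power claim for the primary outcome, and the reader can only check it against the two spreads it cites. Those spreads differ by a factor of about 2.5 (367/144). Which of them is used, and how they are combined, decides whether the claim is true.

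The value of 144 was seen after treatment, at a mean of 882 and after a fall of 1606 − 882 = 724 pg/mL. The design targets a fall about one third as large (250/724 = 0.35), and the placebo arm is not expected to show that fall. So 144 may not describe either arm under the effect being sized for.

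If the 80% is taken at face value, a null result may be read as stronger evidence against a 250 pg/mL effect than the design can give.

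**Working it through.** **Inputs from the Protocol.** 40 recruited, 10% withdrawal, 80% power, alpha 0.05, difference about 250 pg/mL, cited spreads 367 and 144 (Introduction, sample size); two arms (Patient Allocation).

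**Assumptions.** Allocation is 1:1, the brackets are SDs, the test is two-sided, and the analysis is an unadjusted between-arm t-test.

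**Evaluable number.** 40 × 0.9 = 36, so 18 per arm.

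**Power formula.** The noncentrality is δ / (SD × √(2/n)) with 2n − 2 = 34 degrees of freedom, and the two-sided 5% critical value is t = 2.032. At n = 18, √(2/18) = 1/3, so the noncentrality is 3 × 250/SD = 750/SD.

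**Recovering the stated N.** The plain average of the SDs is (367 + 144)/2 = 255.5. The noncentrality is 750/255.5 = 2.94 and power is 81.4%. The smallest n per arm reaching 80% is 18, giving 36 evaluable and 36/0.9 = 40 recruits. This matches the Protocol exactly, but it is a reconstruction; the text does not state the step.

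**SD at which the claim is true.** Solving for 80% power at 18 per arm and 250 pg/mL gives SD = 260 (268 by the normal approximation).

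**Correct pooling.** Variances are averaged, not SDs: √((367² + 144²)/2) = √((134,689 + 20,736)/2) = 278.8.

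**Power at 18 per arm for 250 pg/mL, two-sided t:**

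| SD | Basis | 750/SD | Power | Detectable difference at 80% power (pg/mL) |
|---|---|---|---|---|
| 255.5 | plain average of SDs | 2.94 | 81% | 246 |
| 260 | SD that gives exactly 80% | 2.88 | 80% | 250 |
| 278.8 | correctly pooled | 2.69 | 74% | 268 |
| 367 | pre-treatment SD in both arms | 2.04 | 51% | 353 |

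An unequal-variance t-test with 367 in one arm and 144 in the other gives 73%, close to the pooled result. The normal approximation gives 77% at 278.8 and 53% at 367.

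**Recruits needed for 80% power at 250 pg/mL with 10% withdrawal.** SD 278.8 needs 21 per arm, and 42/0.9 rounds up to 47 (45 by the normal formula). SD 367 needs 35 per arm, and 70/0.9 rounds up to 78 (76 by the normal formula).

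**Routes back to 80%:**

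- *One-sided test.* 84% at SD 278.8, but 64% at SD 367.
- *Baseline adjustment.* The residual SD is SD × √(1 − r²), which must fall to 260. At SD 278.8 this needs r of about 0.36 (81% power at r = 0.4). At SD 367 it needs about 0.71 (79% power at r = 0.7). No correlation is given.
- *Within-arm paired test.* With an SD of change of 367, 18 participants give 78% and 19 give 80%. This also lands near the stated size, but it is not the randomised comparison.

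**The case against.** The strongest reply is that the stated N can be obtained from the cited figures and that the gap is small. The plain average of the SDs returns 40 with the withdrawals included. The text also says only that the change is in the order of 250, and with correct pooling the detectable difference is 268 pg/mL, about 7% higher. On that reading the paragraph is imprecise rather than badly wrong. This stands, and it limits the severity. It does not make averaging SDs valid.

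The 51% is also not a figure the document fixes. It needs the pre-treatment SD in both arms, the brackets to be SDs, a two-sided test and no use of baseline. How far the spread shrinks with a smaller fall is a judgement, and 144 is the only treated value cited. Since sputum is collected at randomisation and again during treatment, a baseline-adjusted analysis is plausible and could reach 80%. This stands too, though the Protocol names neither such an analysis nor a correlation.

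A reader might infer that the trial's power is simply 51% to 74%, or that 40 leaves no room for withdrawals. The documents do not support either. Power depends on choices the text leaves open: two-sided change scores built from 367 and 144 with zero correlation give 46%, while other variants exceed 80%. The reconstruction with the averaged SD does include the withdrawals. Nor is the trial too small for the effect it cites: power for a 724 pg/mL difference exceeds 99% even at SD 367.

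**Conclusion.** The 80% claim is not supported as written. With 18 evaluable per arm and a two-sided, unadjusted between-arm t-test, it holds only for an SD of at most about 260 pg/mL. The Protocol neither states that SD nor justifies it against its own pre-treatment figure of 367. The stated N is recovered by a pooling step that is not valid.

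The shortfall ranges from modest to large. At the correctly pooled SD of 279, power is about 74% and the detectable difference about 268 pg/mL. With 367 in both arms, power is about 51% and the detectable difference about 353 pg/mL. These figures assume 1:1 allocation and that the brackets are SDs; if they are standard errors, the SDs are larger and power is lower. A one-sided test with the pooled SD, or a baseline correlation of about 0.4 at SD 279 or about 0.7 at SD 367, would bring power to about 80% or above. The text relies on none of these.

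This should be fixed. The arithmetic is firm; which SD applies cannot be settled from the document.

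**What to change.** Keep 40 recruits and reword the sample size paragraph so that it:

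- says what the bracketed values are and which SD is used, with the reason;
- states that the test is between arms and two-sided, and that 36 evaluable participants means 18 per arm;
- replaces the 80% claim for 250 pg/mL with the difference detectable at 80% power over the plausible SD range: about 270 pg/mL at SD 279 to about 350 pg/mL at SD 367, unadjusted;
- if a baseline-adjusted analysis is intended, states the baseline correlation relied on and its source.

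The new text should not present 350 pg/mL at SD 367 as the only answer, since the document does not establish that SD for both arms.

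The cost is one paragraph and a less favourable stated sensitivity. No extra participants are needed. Even the upper end, about 350 pg/mL, is about half of the 724 pg/mL fall cited (350/724 = 0.48). Keeping 80% power at 250 pg/mL unadjusted would instead take about 45 to 47 recruits at SD 279, or 76 to 78 at SD 367.

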### **Study Objectives**

To measure the effect of the addition of oral azithromycin treatment in participants with neutrophilic airway disease

1. The intensity and pattern of airway inflammation as assessed by total cell count, cellular differential and cytokine levels present in induced sputum.
2. Clinical status as measured by symptom scores, quality of life measures and pulmonary function tests.
3. Alteration in bacterial load

To determine the rate and inflammatory pattern of exacerbations in participants with neutrophilic airways disease over 6 months

### *Hypothesis*

AZM therapy will reduce interleukin (IL)-8 levels, bacterial load and consequently neutrophilic inflammation in participants with neutrophilic airway disease.

## **Study Design**

This is a double blind placebo controlled study. This study will last for 6 months and involve a minimum of 6 visits to the research unit and telephone consultations.

[figure not shown]

## **Participant Selection**

### *Inclusion Criteria*

- Diagnosis of symptomatic airway disease (asthma or COPD)
- Male or Female over the age of 55 years
- No change in treatments for respiratory disease for 1 month prior to randomisation
- Informed consent obtained
- Increased neutrophils ( $>61\%$  or  $>162 \times 10^4 / \text{mL}$ ) on two occasions (at least one during run-in)
- $\text{FEV}_1/\text{FVC}$  ratio  $<70\%$  AND  $\text{FEV}_1\%$  predicted  $<80\%$
- Ex-smokers should have a KCO% predicted  $>65\%$

### *Exclusion Criteria*

Participants with any of the following will not be included in the study

- $\text{FEV}_1 < 0.5 \text{ L}$
- Current smoking
- Treatment with any macrolide in the preceding month
- Treatment with tetracycline in the preceding month
- Treatment with any oral corticosteroid in month prior to study
- Change in symptom preventer or controller medication in the previous month
- Hypersensitivity to macrolides
- Taking antacid treatment
- Other respiratory diseases including a primary diagnosis of bronchiectasis, pulmonary fibrosis, pulmonary vascular disease or lung cancer
- Inability to attend study visits

- Respiratory tract infection during month prior to randomisation
- Respiratory exacerbation during month prior to randomisation
- Impaired liver function at Visit 2 as shown by AST, ALT, alkaline phosphatase or total bilirubin greater than the 2 times upper limit of normal

### *Study Population*

Participants will be recruited from the Respiratory clinic at John Hunter Hospital. Participants must have a diagnosis of neutrophilic airway disease.

### **Study Medication**

Azithromycin (Zithromax) and identical placebo tablets will be prepared by a compounding pharmacy and delivered to the Pharmacy department of the John Hunter Hospital.

### *Packaging, Storage, Dispensing and Accountability*

The Pharmacy Department of the John Hunter Hospital will be responsible for the packaging of study medication. Tablets will be packaged in glass bottles (brown) that will be labeled with the study name and the instructions for the participant. The medication will be stored securely in the Pharmacy Department and will be dispensed on presentation of a hospital script according to the randomisation schedule.

### *Patient Allocation*

Patients will be randomly allocated to either receive placebo or AZM 250mg daily. They will take the medication for twelve weeks. Both the participant and the investigators will be blinded to the intervention until the conclusion of the trial. The placebo and agent will be packaged similarly and have identical taste. The use of other medications will be assessed at the commencement of the trial and updated with each contact. The patient will be asked about all new medications commenced and changes in the use of regular medications. If a participant commences treatment with other antibiotic agents during the study they will be withdrawn from the study. To aid compliance medication will be dispensed at each visit. Participants will also be questioned about compliance during the regular phone review.

Treatment will be randomised using random permuted blocks of 6. The data manager in the respiratory research unit using the Randomisation Generator Software (11) will generate the randomisation allocations. The randomisation tables for each stratification list will be

provided to the pharmacy department who will dispense active or placebo medication according to the schedule. The investigator and research team working with the participants will not have access to the randomisation schedule during the study.

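### Withdrawing from the study anyone who starts another antibiotic conflicts with the 6-month exacerbation objective and makes loss outcome-related; the 10% withdrawal allowance may be exceeded

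*Protocol*

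**What the plan says.** The withdrawal rule is in the protocol under Patient Allocation: "If a participant commences treatment with other antibiotic agents during the study they will be withdrawn from the study". It has no time limit within the study, and Study Design sets the duration: "This study will last for 6 months and involve a minimum of 6 visits to the research unit and telephone consultations".

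Three other places bear on it:

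- Study Objectives includes: "To determine the rate and inflammatory pattern of exacerbations in participants with neutrophilic airways disease over 6 months".
- Evaluation of the Study names the primary outcome as "Decrease in sputum IL-8". The secondary outcomes include "Decreased in airway bacterial load", sputum neutrophils and "Number of exacerbations during follow-up".
- The Introduction says participants will be telephoned to "see if they have had an increase in their symptoms or medication use (exacerbation"). Its sample-size paragraph recruits 40, and "this includes a 10% withdrawal rate".

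No section provides for collecting outcomes after this withdrawal, and none separates stopping study drug from stopping follow-up.

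**The concern.** An exacerbation is recognised partly by increased medication use, so a new antibiotic course can be part of an outcome event and also end that person's observation. A 6-month rate cannot be fully observed under such a rule.

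The loss is also unlikely to be random. In asthma or COPD a new antibiotic is plausibly prescribed for infection or exacerbation, so those removed would tend to be the more inflamed. The hypothesis is that azithromycin lowers bacterial load and neutrophilic inflammation. If it does, more placebo than active participants would be removed. Withdrawals before 12 weeks also remove on-treatment sputum, so IL-8, neutrophils and bacterial load are exposed as well as exacerbations. An analysis plan can choose how to handle missing data, but it cannot recover samples and contacts that were never collected.

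**Working it through.** **1. The sections side by side.** The rule applies throughout the study; the study is 6 months; the exacerbation rate is wanted over 6 months. A participant given an antibiotic in month 2 contributes nothing to months 3 to 6. The objective and the rule cannot both be met in full.

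**2. The stated sample size.** Inputs from the Introduction: difference 250 pg/mL, alpha 0.05, power 80%, 10% withdrawal, and 367 and 144 read as SDs. Assumed, because not stated: SD (367 + 144)/2 = 255.5, two-sided t-test, 1:1 allocation.

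- Standardised difference: 250/255.5 = 0.978.
- Required n per arm: 17.41, rounded up to 18, so 36 in total.
- Inflated for withdrawal: 36/0.9 = 40, as stated.

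The allowance is therefore 10% × 40 = 4 participants, for every cause of withdrawal.

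**3. The antibiotic rate that uses up the allowance.** With a constant rate r of first courses, the proportion withdrawn by time T is 1 − exp(−rT). Setting this to 0.10 gives r = −ln(0.9)/T.

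- T = 12/52 year: 0.1054/0.2308 = 0.46 per person-year.
- T = 0.5 year: 0.1054/0.5 = 0.21 per person-year.

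The 12-week figure is the relevant one for the primary outcome, because later losses do not remove on-treatment sputum. The protocol gives no antibiotic rate, so the rates below are assumptions:

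| Assumed first courses per person-year | Withdrawn by 12 weeks | Withdrawn by 6 months | Chance of more than 4 of 40 by 12 weeks |
|---|---|---|---|
| 0.25 | 6% | 12% | 0.071 |
| 0.5 | 11% | 22% | 0.445 |
| 1.0 | 21% | 39% | 0.936 |
| 2.0 | 37% | 63% | >0.99 |

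**4. Power if losses exceed 10%.** 20 randomised per arm, SD 255.5, two-sided t-test:

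| Loss | Evaluable per arm | Power | N needed for 80%, 36/(1 − loss) |
|---|---|---|---|
| 10% | 18 | 81% | 40 |
| 20% | 16 | 76% | 45 |
| 30% | 14 | 70% | 52 |

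With losses of 30% on placebo and 10% on azithromycin (14 and 18 evaluable), power is 76%.

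**5. Exacerbations.** Assume, for illustration, λ = 1.0 expected events over follow-up on placebo and 0.6 on active (true ratio 0.60), and that a fraction p = 0.7 of events leads to an antibiotic. At a constant rate, the mean observed count is (1 − exp(−λp))/p and the mean fraction of follow-up observed is (1 − exp(−λp))/(λp).

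- Placebo: count 0.719, follow-up 0.719, so 0.719/0.719 = 1.00 per unit time.
- Active: count 0.490, follow-up 0.817, so 0.490/0.817 = 0.60 per unit time.

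If everyone within an arm has the same risk, a person-time analysis recovers the true ratio, although 1 − 0.719 = 28% of placebo events are never seen. If risk varies between participants, the recovery fails. With gamma-distributed risk (mean 1, variance v), the mean count is [1 − (1 + vλp)^(−1/v)]/p and the mean follow-up is the integral of (1 + vλpt)^(−1/v) over t from 0 to 1. The person-time ratio becomes 0.63, 0.65 and 0.69 for v = 0.5, 1 and 2. High-risk participants leave first, and more of them leave on placebo.

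**6. IL-8.** A bias estimate would need withdrawal by arm before 12 weeks and the relation between antibiotic use and IL-8. The protocol gives neither, so only a probable direction can be stated.

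**The case against.** **The rule has a rationale.** This is largely a mechanistic trial, and another antibiotic directly alters bacterial load and may alter neutrophils and IL-8. Recent macrolide or tetracycline use is an exclusion criterion for the same kind of reason. This stands: keeping such participants puts affected samples in the main analysis. It justifies setting samples aside in a sensitivity analysis; it does not require losing the person.

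**The trigger is an antibiotic, not an exacerbation.** Events managed without antibiotics stay under observation, and antibiotics for non-respiratory reasons also cause withdrawal. This stands too. The link is partial, and it would be wrong to infer that recurrent exacerbations are never counted.

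**An analysis plan could use person-time.** It could, and that removes the distortion when risk is uniform. A reader comparing raw counts in step 5 would get 0.490/0.719 = 0.68 instead of 0.60, but that comes from ignoring shortened follow-up and is not evidence of bias in a rate analysis. What remains is the smaller effect of varying risk, and the unseen events.

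**Stronger readings of the sample size.** A reader might infer that the 10% allowance is broken. The protocol gives no antibiotic or exacerbation rate, so it is only at risk. A reader using SD 367 would find 41% power at 30% loss, but that SD already gives 51% at the planned 18 per arm. Most of that shortfall is a question about the SD, not about antibiotics.

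**The IL-8 bias is not derived.** This is correct. Any figure would rest on assumed losses and an assumed correlation. An analysis of change, or one adjusted for baseline, could also reduce the effect of selection on severity.

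**Conclusion.** The point holds as a conflict in the protocol's own text, and is should-fix. The antibiotic withdrawal rule cannot be reconciled with a 6-month exacerbation rate, and it makes loss depend on the outcomes and possibly on the arm. Later exacerbations after an antibiotic-treated event go unobserved. On-treatment IL-8, neutrophil and bacterial-load values may be missing selectively. The probable direction is towards no effect, by an amount the documents do not allow to be calculated.

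The allowance of 4 in 40 may be exceeded: antibiotic starts alone reach it at about 0.46 first courses per person-year over 12 weeks. If losses reached 20% or 30%, power would fall from 81% to 76% or 70%. These figures rest on a constant antibiotic rate, SD 255.5, a two-sided test and 1:1 allocation. The direction of bias rests on antibiotics being given mainly for respiratory events and on the trial's hypothesis being true.

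**What to change.** Reconcile Patient Allocation with Study Objectives and Evaluation of the Study, for example with this text:

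*Starting a non-study antibiotic is recorded with its date and reason and does not end study follow-up. Scheduled visits, sputum samples and exacerbation contacts continue. All randomised participants are analysed in their allocated arm, and exacerbations are analysed over actual follow-up time.*

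Add a sensitivity analysis for IL-8, neutrophils and bacterial load that sets aside samples taken during or shortly after a non-study antibiotic course, with the window fixed before unblinding. Setting samples aside partly brings back the selection described above, so this should not be the main analysis.

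Whether study medication continues during such a course is a clinical matter and is not addressed here.

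Cost: a short amendment and a case report form field for antibiotic date and reason. The visits and contacts are already scheduled. The downside is that some sputum values in the main analysis will be affected by non-study antibiotics. If placebo participants receive more of them, that may itself attenuate the contrast.
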